#### Inclusion criteria

Patients will be included in the study if they are displaced victims of interpersonal violence, aged 18 years or older, if they have PTSD as a primary diagnosis established by a psychiatrist or clinical psychologist during intake, if individual NET in an outpatient setting has been indicated for them and if they are cognitively able to give informed consent to participate in the study.

#### Exclusion criteria

Patients will be excluded from the study if they display signs of an acute crisis, such as acute suicidality or acute severe psychosis, or suffer from persistent substance abuse. These exclusion criteria are applied because of their expected disturbing influence on the adherence and/or completion of NET.

#### Recruitment

This is an ongoing treatment trial. The enrolment period is planned to run for 2.5 years from February 2018 to January 2021. Following multi-disciplinary clinical assessment and evaluation, the diagnosis and treatment indication will be discussed with patients. Those who are eligible for enrolment will be informed about the study and will be invited to participate. This eligibility will be considered as broadly as possible within the inclusion criteria to allow for a representative sample of displaced victims of interpersonal violence. Information about the study aims and objectives, guarantee of anonymization of data and the fact that participants are free to terminate participation at any moment will be given orally and provided on paper through an information leaflet. After, intake patients are placed on a waiting list for NET, ranging from 1 to 4 months. When patients from the waiting list are invited to start NET, they will once again be informed about the study orally and on paper. Patients will be asked to consider participation over a minimum period of 3 days. Afterwards, they will be contacted by phone or face-to face and given ample opportunity to ask additional questions. If they indicate willingness to participate in the study, an appointment is made to sign informed consent and conduct the baseline assessment (T0). Participants are invited to bring someone they trust to this meeting. Participants will be receiving a voucher of 10 euros after the follow-up measurement. If after the first year the aspired total number of participants seems unachievable, prolongation of the enrolment period and multicentre options will be explored after consultation with the involved medical ethical committee.

### Intervention

#### Narrative exposure therapy

NET is an evidence-based short-term psychotherapy targeting PTSD symptoms, specifically appropriate for multiple traumas in divergent cultural settings. For the study population in question, the method is found to be feasible [36] and is considered the first choice TFT [33]. The NET protocol includes 12–16 sessions of individual trauma focused exposure, performed weekly or twice a week by trained mental health professionals. Each session lasts 90–120 min, depending on the content of the trauma which is targeted during the session, and the possible involvement of an interpreter. NET aims to create a chronological narrative of a patient’s life story, including both traumatic and empowering memories. During each session, one or more significant memories (traumatic or empowering) are discussed in great detail. Imaginary exposure, meaning-making, and reprocessing are used to reduce PTSD symptoms. An account of each session is written down by the therapist, which will result in a patient’s biography when the therapy has been completed.

#### Co-interventions before and during treatment

When participants cannot immediately start NET, there are no restrictions in psychological or pharmacological interventions received during their waiting period, applied in accordance with the national guidelines. Such interventions can be indicated either for symptom management or as a preparation of individual TFT. In addition, individual sessions can be provided in case of (imminent) crisis. From the start of NET onwards, however, no other modules will be provided, unless in case of acute crisis in which the safety of a participant is endangered or he/she is about to harm others. Previously started pharmacological interventions can be continued during NET; however, no new pharmacological interventions will be started during NET.

#### Discontinuation of the intervention and drop-out

Discontinuation of NET will take place if patients so wish or if multi-disciplinary clinical evaluation indicates that continuation is not in the best interest of the patient. If patients wish to stop participating in the study but wish to continue NET, this will be allowed. Patients will be considered dropouts when there are deviations from the NET treatment protocol for more than four consecutive sessions (i.e. no trauma-focused approach during the sessions or no-show), since in these cases the effectiveness of the treatment offered cannot be assured [34].

### Measurements

#### Perceived Stress Scale (PSS)—full scale administered pre-and post-treatment

The PSS [37] has been developed to measure the perception of daily stress by assessing how unpredictable, uncontrollable and overloading patients experience daily life. With 10 items, thoughts and feelings and the evaluation of daily life in the last month are explored through a 5-point scale ranging from 0 to 4. Mean scores will be calculated, ranging from 0 to 4. Example item: ‘In the last month, how often have you been upset because of something that happened unexpectedly?’ Administration of the questionnaire takes approximately 10 min. Acceptable psychometric properties of the instrument have been established [38].

#### Subscale administered before each session

The four items version of the PSS [39] will be administered at the start of each session. These items have proven sensitivity to short-term changes in stress [40]. For the purpose of this study, the indicated timespan was changed from ‘In the last month’ to ‘In the last week’ to match the other pre-sessions measures for possible predictors. An example item is ‘In the last week, how often have you felt that things were going your way?’ These items will be scored on a VAS-scale of exact 10 cm by placing a cross on a line from 0 (not at all) to 100 (completely). Mean scores will be calculated, ranging from 0 to 100.

#### Difficulties in Emotion Regulation Scale short version–18 (DERS)—full scale administered pre- and post-treatment

The DERS was developed to measure emotion regulation. The DERS-18 comprises 18 items and uses a 5-point Likert scale ranging from 1 to 5; it has 6 subscales: non-acceptance of emotional responses, difficulty engaging in goal-directed behaviour, impulse control difficulties, lack of emotional awareness, limited access to emotion regulation strategies and a lack of emotional clarity. Mean scores will be calculated, ranging from 1 to 5. Example item: ‘I pay attention to how I feel’*.* Administration of the questionnaire takes approximately 10 min. The DERS has high internal consistency, good test-retest reliability, moderate construct and predictive validity [41].

#### Subscale ‘impulsivity’ administered before each session

As a proxy of emotion regulation, the subscale ‘Impulsivity’ will be used, comprising three items from the ‘Difficulties in Emotion Regulation Scale’ (DERS-18; 40). For the purpose of this study, the phrase ‘In the last week I have felt:’ was added to match the other pre-session measures for possible predictors. Example item: ‘When I am upset, I become out of control’. Items will be scored on a VAS-scale ranging from 0 (not at all) to 100 (completely)*.* Mean scores will be calculated, ranging from 0 to 100.

#### PTSD Checklist for DSM-5 (PCL-5)—administered pre-and post-treatment

The 20 item PCL-5 is a self-report checklist which measures the presence and severity of the 20 DSM-5 symptoms of PTSD on a 5-point scale (0–4) (e.g. ‘Trouble remembering important parts of the stressful experience’)*.* Mean scores will be calculated, ranging from 0 to 4. It will be used to indicate PTSD symptom severity pre- and post-treatment. Administration of the questionnaire takes approximately 10 min. The instrument has good psychometric quality [42].

#### Primary Care Post-traumatic Stress Disorder (PCPTSD)—administered before each session

Because a short version of the PCL-5 is unavailable, the five-item Primary Care Post-traumatic Stress Disorder (PCPTSD) checklist was selected to increase the feasibility of the frequently repeated measurements. This questionnaire is used to measure PTSD symptoms [43]. For the purpose of this study the indicated timespan was changed from ‘In the past month, have you’ to ‘In the last week’ to match the other pre-session measures for possible predictors. An example item is: ‘In the last week did you have nightmares about the event(s) or thoughts about the event(s) when you did not want to?’ These items will be scored on a VAS-scale ranging from 0 (not at all) to 100 (extremely). The questionnaire has good psychometric qualities [41]. Mean scores will be calculated, ranging from 0 to 100.

#### Mood—measured before each session

Mood will be measured using a validated single item measure [44]. For the purpose of this study, we have altered the item ‘At the moment I feel’ to ‘In the last week I felt’ to make the timespan congruent to the other pre-session measures for possible predictors. This mood item will be scored on a VAS-scale ranging from 0 (sad) to 100 (happy). Mean scores will be calculated, ranging from 0 to 100.

#### Critical incidents

Before each therapy session, the client will be asked to report if any relevant personal circumstances have arisen since the last appointment.

#### Other

Biographical data of patients will be collected (i.e. gender, age, educational level, current residence, legal status, country of birth) to describe the study population.

#### Questionnaire on Process of Recovery Short Version–15

The QPR is a 5-point scale (0-4), self-report questionnaire that probes people’s recovery and meaningful aspects in the recovery process (e.g., ‘I feel able to take chances in life.’). The QPR-15 consists of 15 items. Mean scores will be calculated, ranging from 0 to 4. The questionnaire has good psychometric properties, and has proven to be associated with quality of life, empowerment, and psychological wellbeing [45]. Administration of the questionnaire lasts approximately 20 minutes. The questionnaire has been selected because it represents psychological wellbeing beyond the scope of mental health symptoms. The QPR is reliable and valid, and has proven to be associated with quality of life, empowerment and psychological wellbeing [45].

#### Early Trauma Inventory–short version

The Early Trauma Inventory–short version (ETI-SF) was developed to determine potentially traumatic events before and after the age of 18 years old [46]. The ETI-SF comprises 27 items that assess physical, emotional, and sexual abuse. Items vary between open questions and multiple choice being answered with yes or no. The scale has a range from 0 to 29, with higher scores referring to a higher number of traumatic experiences. Administration of the questionnaire lasts approximately 10 min. Its reliability and validity are good [47]. The questionnaire has been selected to describe trauma-related features of the study population.

#### Life Events Checklist (LEC–5)

The LEC-5 comprises 17 multiple choice items on a 6-point nominal scale (i.e., ‘happened to me’, ‘witnessed it’, ‘learned about it’, ‘part of my job’, ‘not sure’, ‘doesn’t apply’). The checklist aims to determine whether someone has ever been exposed to 16 events known to potentially result in PTSD or distress, and one additional event not captured in the first 16 items. In the last part of the LEC-5, respondents are asked which event he/she considers to have had the most impact, followed by 7 questions, both open- and multiple-choice questions, aimed at identifying the characteristics of this event. The scale has a range from 0 to 68, with higher scores referring to a higher number of traumatic experiences. Administration of the questionnaire lasts approximately 20 min. The reliability of the LEC-5 is considered to be good [48]. The questionnaire was selected to describe trauma-related features of the study population.

### Data collection, management and analysis

#### Procedure pre-session measures

During baseline (T0) and at the start of each TFT session, the patient’s fixed practitioner or a supervised master’s level psychology student will administer the thirteen items selected to assess the four abovementioned possible predictors. To avoid an order effect, the sequence of the measures for possible predictors and the order of questions within every measure will change with every session. These measures will only be administered during the treatment period. They will be administered by pen and paper and are expected to take on average 10 min. Questionnaires are translated from their original English version according a forward-backward procedure by two independent native speakers into Dutch, and by professional translators into Arabic, French, Amharic and Tigrinya. Interpreters will assist for other languages.

#### Procedure pre- and post-treatment

During baseline (T0), post-treatment (T1) and follow-up (T2) measurements, the abovementioned set of questionnaires will be administered. See Fig. 1 for a detailed overview of the planned time points for assessments. These questionnaires will be administered digitally and are expected to take a maximum of 80 min. Questionnaires are available in Dutch and English. Given the lack of computer skills and the often limited Dutch and/or English proficiency within the study population, a clinician and interpreter will be available for assistance. Measurements will take place at the treatment location; if preferred, this meeting will be combined with other appointments. After the last assessment, participants will receive a voucher of 10 euros.

### Statistical analysis

First, multiple regression analyses and logistic regression analyses will be performed to examine whether high perceived daily stress, emotion dysregulation and low mood at baseline predict drop-out, no-show and treatment outcomes. Secondly, the concurrent association between each possible predictor measured prior to each session (i.e. perceived daily stress, emotion regulation and mood) and PTSD symptoms will be examined using bivariate (multilevel) growth modelling, as multiple observations of the predictor variables and PTSD symptoms (level 1) are nested within individuals (level 2) [49]. In order to infer that change in the predictor variables leads to change in PTSD symptoms, we will examine the timeline (i.e. temporal precedence) in two ways [50, 51]. The dynamic (i.e. temporal) associations will be examined by estimating whether change in PTSD symptoms from the previous week to the current week (t) can be predicted by change of a possible predictor at the previous week (t-1) using multilevel modelling. To examine the timeline of larger shifts instead of week-to-week changes, it will be examined whether the earliest significant decrease in mean levels of each possible predictor (improvement) occurs before the largest reduction in mean levels of PTSD symptoms.

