In the present paper, the feasibility, rationale and protocol of an ongoing trial are described. Specifically, we aim to identify relevant predictors of PTSD symptom change during and after NET in 80 displaced victims of interpersonal violence. The primary hypotheses of the study are (1) it is feasible to administer highly repeated measures, within a diverse group of displaced persons. (2) High perceived daily stress, emotion dysregulation, and low mood at baseline and during NET predict higher drop-out, higher no-show and poorer treatment response of NET (i.e. less PTSD symptom reduction), thus undermining the feasibility of NET; (3) Reduction in perceived daily stress and improvement in emotion regulation and mood during NET are associated with concurrent reductions in PTSD symptoms during NET; (4) Change in perceived daily stress, emotion dysregulation, and mood during NET predict subsequent changes in PTSD symptoms at later stages of NET. Furthermore, the study aims to establish whether NET contributes to positive aspects of mental health.

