### Participants

The study will take place at an outpatient clinic specialized in mental health care for refugees, asylum seekers, victims of sexual exploitation and otherwise traumatized populations in the Capital region in the Netherlands. The study aims to include 80 participants, in order to detect medium to small effect sizes [35]. Patients are referred to the clinic by a general practitioner or by a partnering social welfare organization. Patients’ background/nationality is diverse; most originate from West Africa, the Middle East and Eastern Europe. Their legal status varies from having obtained a residence permit or even Dutch citizenship to illegal residence in the country, and they may reside in asylum seekers centres, specialized shelters for victims of sexual exploitation, governmental shelters for illegal persons or live independently.

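### The stated regression of treatment response on baseline stress, dysregulation and mood names no baseline PTSD severity and fixes neither change nor post score, so severity alone can create or mask an association

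*Protocol article*

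**What the plan says.** The Statistical analysis section states the model for the baseline part of hypothesis 2. Multiple and logistic regressions are to test, with perceived stress as the further regressor, whether "emotion dysregulation and low mood at baseline predict drop-out, no-show and treatment outcomes". Three regressors are named. When the same section moves on to the session-level models, it again limits the possible predictors to stress, emotion regulation and mood, with PTSD symptoms as the outcome.

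Hypothesis 2 in the Background defines the outcome as "poorer treatment response of NET (i.e. less PTSD symptom reduction", which is a quantity that depends on where a patient starts. The analysis section says only "predict drop-out, no-show and treatment outcomes" and does not choose between a change score and a post-treatment score.

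Baseline severity is measured. Of the PCL-5 the Measurements section says: "It will be used to indicate PTSD symptom severity pre- and post-treatment". The Abstract and the procedure section place the main questionnaires at T0, T1 and T2.

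One section counts differently. Procedure pre-session measures refers to "thirteen items selected to assess the four abovementioned possible predictors". Thirteen items is 4 (PSS) + 3 (DERS impulsivity) + 5 (PCPTSD) + 1 (mood), so the fourth predictor in that count is PTSD itself. The Background also lists PTSD beside the other three among the factors that may affect feasibility.

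**The concern.** The Background says that daily stressors are associated with PTSD symptoms, that emotion dysregulation mediates the development of PTSD, and that depression and PTSD are often comorbid. The three regressors are therefore expected to carry information about baseline PTSD severity. Severe patients have more room to improve and regress towards the mean, so on a change score a marker of severity looks favourable. They also tend to remain higher afterwards, so on a post score the same marker looks harmful. Neither result shows that stress, dysregulation or mood predicts response beyond severity.

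Hypothesis 2 is one of the primary hypotheses, and the Discussion goes further than crude prediction. It speaks of the impact of these factors on PTSD change. It would use positive results to support work on stress or emotion regulation before NET, and null results to encourage offering trauma-focused therapy despite such problems. The first use is exposed to confounding by severity, the second to masking.

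**Working it through.** **Sample size.** The plan says: "The study aims to include 80 participants, in order to detect medium to small effect sizes". Alpha, power and a numeric effect size are not given, so 80 cannot be reproduced. Assuming two-sided 0.05 and 80% power (noncentral F, lambda = f² × N), the joint test of three predictors at f² = 0.15 needs 77, and one coefficient at f² = 0.10 needs 81. The figure of 81 is the same with three or four terms in the model, so a baseline covariate does not raise the sample size for a single coefficient.

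**Inputs for the bias check.** N = 80 is from the plan. The rest is assumed, because the documents give no coefficients:
- r, the correlation of each predictor with baseline PTSD: 0.3 to 0.6
- rho, the pre-post PTSD correlation: 0.4 to 0.6
- correlation between any two predictors: 0.4

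All predictors are standardised and scored so that higher is worse.

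**Expected coefficients.** Regressing baseline PTSD on the three predictors gives each a slope of r / (1 + 2 × 0.4) = r / 1.8. Let post = rho × pre + d × X1 + error, where d is the true effect of one predictor given baseline. Without baseline PTSD in the model:
- post score: coefficient of X1 = d + rho × r / 1.8
- reduction (pre minus post): coefficient of X1 = −d + (1 − rho) × r / 1.8

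With d = 0 and r = rho = 0.5, both equal 0.5 × 0.5 / 1.8 = 0.139. On the post score this reads as harm, on the reduction as benefit. Simulated means were 0.138 and 0.141. With baseline PTSD in the model they were about zero.

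**False-positive rates with d = 0** (2,000 simulated trials per scenario, two-sided 0.05). Joint test of the three predictors without baseline PTSD:

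| r | rho | Change score | Post score |
|---|---|---|---|
| 0.3 | 0.4 | 32% | 16% |
| 0.3 | 0.6 | 22% | 39% |
| 0.5 | 0.5 | 67% | 69% |
| 0.6 | 0.4 | 93% | 64% |
| 0.6 | 0.6 | 76% | 97% |

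With baseline PTSD the joint rate is 4% to 6% throughout. For a single coefficient the range is 8% to 40% without it and 4% to 6% with it.

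**Masking.** Take d = 0.25 and rho = 0.5 on a change score:
- r = 0.3: −0.25 + 0.5 × 0.3 / 1.8 = −0.167. Power is 26% without baseline PTSD and 58% with it.
- r = 0.5: −0.25 + 0.5 × 0.5 / 1.8 = −0.111. Power is 15% without and 55% with.

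On a post score the same effect is inflated instead, to 0.25 + 0.083 = 0.333 and 0.25 + 0.139 = 0.389.

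**The case against.** **The omission is read from silence.** No sentence says that baseline PTSD is left out. The text is a condensed article, a full plan could name the covariate, and the four-predictor count includes PTSD. A reader might infer that the study has decided against adjustment, and the documents do not support that. What stands is narrower: the stated model lists three regressors, the same section repeats that list, and the four-predictor count conflicts with it.

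**A larger effect is tempting.** With one predictor alone and both correlations at 0.5, its correlation with change or post score is 0.25 in absolute value. That is significant in about 61% of trials at N = 80, and a true adverse effect of 0.25 SD can even change sign. A reader might infer that the sign of the result is decided by the choice of outcome. The plan describes multiple regression on three predictors. There the single-coefficient rate is 8% to 40%, and an effect of 0.25 is attenuated in the scenarios shown but not reversed. The sign can depend on the outcome chosen; it need not.

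**The null favours adjustment.** The rates assume no predictor effect given baseline severity. If instead a single predictor is unrelated to change, then at correlations of 0.5 and 0.5 the baseline-adjusted coefficient is (0.5 − 0.5 × 0.5) / (1 − 0.5²) = 0.33, significant in about 86% of trials at N = 80. In a non-randomised predictor study, change score and baseline adjustment answer different questions, and a crude association remains valid as crude prediction. This limits what the adjusted estimate means, so the target must be stated. It does not defend an unadjusted model with an unfixed outcome whose results are to guide treatment.

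**The correlations may be low.** All patients have PTSD as primary diagnosis, which may restrict the range of severity. At r = 0.3 the joint false-positive rate is still 16% to 39%.

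**Conclusion.** The point holds in this form: the hypothesis 2 regression is stated with baseline stress, dysregulation and mood only, without T0 PCL-5 and without fixing change or post score. Baseline severity can then create an association with response or weaken a true one. Under the assumed correlations the joint false-positive rate is about 16% to 97% against 4% to 6% with adjustment, and 8% to 40% against 4% to 6% for one coefficient. A true effect of 0.25 SD on a change score shrinks to about 0.11 to 0.17 (r = 0.5 and 0.3, rho = 0.5). These figures show direction and order of size only. They rest on assumed correlations and on a null of no effect given baseline severity.

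The change-versus-post argument concerns treatment response. It does not carry over to drop-out and no-show, where the issue would be confounding by severity, and that was not quantified. The model should be corrected before analysis; confidence is moderate, because a fuller plan may already name the covariate.

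**What to change.** - Analyse T1 and T2 PCL-5 with T0 PCL-5 as a covariate and the three baseline predictors entered together.
- State that the estimand is prediction of response beyond baseline severity, and report the unadjusted association beside it, labelled as crude prediction.
- Reconcile the three predictors of the Statistical analysis section with the four in Procedure pre-session measures, and say what role PTSD has.
- Adding T0 PCL-5 to the drop-out and no-show models is optional and depends on the number of events.

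The cost is one degree of freedom and no new data, since PCL-5 is already taken at T0. The downside is that the main estimate becomes conditional on baseline severity, which is why the crude association should be kept alongside. The article reports that no analysis had been performed when it was written, so at that stage the model could be fixed without sight of results.

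### The lagged change-on-change model has session t-1 on both sides and is described in one direction only, so it can mask or reverse the effect that hypothesis 4 looks for

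*Protocol article*

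**What the plan says.** Hypothesis 4 (protocol article, Background) is directional: "Change in perceived daily stress, emotion dysregulation, and mood during NET predict subsequent changes in PTSD symptoms at later stages of NET".

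The Statistical analysis section gives the purpose as "In order to infer that change in the predictor variables leads to change in PTSD symptoms" and names two timeline checks. The first is a week-to-week multilevel model, which asks whether "change in PTSD symptoms from the previous week to the current week (t) can be predicted by change of a possible predictor", with the predictor change dated one week earlier, at t-1. The second compares larger shifts, asking whether the "earliest significant decrease in mean levels of each possible predictor (improvement) occurs before the largest reduction in mean levels of PTSD symptoms". Both look only for predictor before PTSD.

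Under Procedure pre-session measures, the items are given together: "During baseline (T0) and at the start of each TFT session", staff "administer the thirteen items selected to assess the four abovementioned possible predictors". The count of thirteen works only if PTSD is included: 4 stress + 3 impulsivity + 5 PTSD + 1 mood = 13. All are 0 to 100 visual analogue ratings. Higher is worse for PTSD and impulsivity, and the stress score is treated here in the same sense. Mood runs from sad (0) to happy (100).

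**The concern.** On the natural reading, the outcome is P(t) - P(t-1) and the predictor is X(t-1) - X(t-2), where P is the session PTSD score and X is a predictor. P(t-1) and X(t-1) come from the same form. If a patient reports an unusually bad week at session t-1, the predictor change is pushed up. The PTSD starting point is pushed up too, so the next PTSD change tends to be downward. The model reads this as rising stress followed by falling PTSD.

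Hypothesis 3 expects a concurrent association between predictor change and PTSD change, and shared reporting error would add to it. The Discussion says the PTSD and dysregulation items are not validated for weekly repetition.

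Two things are at stake. A real lagged effect could be shrunk, hidden or given the wrong sign. And a claim about what drives what would rest on a comparison described in one direction only. Masking is not harmless here, because the Discussion gives a null result a clinical reading: it might encourage clinicians to offer trauma-focused therapy despite these difficulties.

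**Working it through.** **Plan's own figure.** The article gives no number for the lag model. Its only planning figure is 80 participants, with no alpha, power or numeric effect size, so there is nothing to reproduce.

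**Inputs from the article.** 80 patients; 12 to 16 sessions (14 used below); same-sitting measurement. Not given, and so assumed: within-session correlation, autocorrelation, and the share of within-person variance that is session error.

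**General result.** Let G(k) = Cov(P(t), X(t-k)) within person. Then

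Cov(P(t) - P(t-1), X(t-1) - X(t-2)) = 2G(1) - G(0) - G(2),

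and the slope is this divided by Var(X(t-1) - X(t-2)). It takes the sign opposite to a positive G(0) whenever G(0) + G(2) > 2G(1).

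**No lagged effect, autocorrelated scores.** With equal SDs, correlation rho within session and autocorrelation phi, G(k) = rho·phi^k and the variance of the difference is 2(1 - phi). The slope is -rho(1 - phi)/2. The last column comes from simulation with complete data and patient-clustered standard errors, used as a stand-in for the multilevel model.

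| rho | phi | Slope | Share significant |
|---|---|---|---|
| 0.2 / 0.4 / 0.6 | 0 | -0.10 / -0.20 / -0.30 | 76-77% / 100% / 100% |
| 0.2 / 0.4 / 0.6 | 0.3 | -0.07 / -0.14 / -0.21 | 49% / 97-98% / 100% |

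**No lagged effect, correlated session error.** With error share w, error correlation r and uncorrelated underlying states, the slope is -w·r / [2w + 2(1 - w)(1 - phi)].
- w = 0.5, r = 0.5, phi = 0.5: -0.25/1.5 = -0.167 (simulated -0.168, significant in 99%).
- w = 0.5, r = 0.3, phi = 0.5: -0.15/1.5 = -0.10 (simulated -0.101, 78%).
- w = 0.3, r = 0.3, phi = 0.7: -0.09/1.02 = -0.088 (simulated -0.084, 65%).

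**Where it vanishes.** With errors and states uncorrelated across scales, the simulated slope is -0.002. With random-walk states and uncorrelated errors it is -0.001.

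**Mood.** Reversing the scale gives +0.166, significantly positive in 100%. Hypothesis 4 expects a negative sign for mood, so this too runs against it.

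**True lagged effect of 0.15** (phi = 0.3, unit innovation variance, innovations correlated rho). Var(X) = 1/0.91 = 1.099 and Var(X(t-1) - X(t-2)) = 2 × 1.099 × 0.7 = 1.538.
- rho = 0.3: G(0) = (0.3 + 0.0495)/0.91 = 0.384; G(1) = 0.3 × 0.384 + 0.15 × 1.099 = 0.280; G(2) = 0.3 × 0.280 + 0.0495 = 0.133. Slope = (0.560 - 0.384 - 0.133)/1.538 = 0.03. Simulated power is 13 to 16%.
- rho = 0.6: G(0) = 0.714, G(1) = 0.379, G(2) = 0.163. Slope = (0.758 - 0.714 - 0.163)/1.538 = -0.08, so the sign is reversed.

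**True lagged effect of 0.3** (30% session error, phi = 0.5). The simulated slope falls from +0.137 at error correlation 0 (96% significantly positive) to +0.067 at 0.3 (46%) and +0.016 at 0.5 (6%).

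**Only PTSD drives the predictor (0.20).** With phi = 0.3 and rho = 0.3: G(0) = 0.402, G(1) = 0.121, G(2) = 0.036, and the variance of the predictor difference is 1.519. The forward slope is (0.241 - 0.402 - 0.036)/1.519 = -0.13, matching the simulated -0.13 (significant in 95 to 96%). The forward model alone does not reveal that the effect runs the other way.

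**Simple corrections, no lagged effect** (w = 0.5, r = 0.5, phi = 0.5):

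| Model | Slope | Significantly negative |
|---|---|---|
| As described | -0.168 | 99% |
| Plus raw P(t-1) and time | -0.107 | 93% |
| Plus person-centred P(t-1) and time | -0.023 | 15% |
| Plus previous PTSD change | -0.033 | 18% |
| Reverse: X change on prior P change | -0.166 | 100% |

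A lagged-level model centred on observed person means can err the other way. With half session error uncorrelated across scales and state correlation 0.5, it gave +0.061 with no lagged effect, falsely supporting hypothesis 4 in 45% of runs.

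**The case against.** The article is condensed and gives the lag model one sentence. It names no covariate, centring, time trend or error structure, and excludes none. A reader might infer that prior PTSD will be left out, or that the reverse path will never be fitted. The documents do not support either: these things are not described, but they are not ruled out. What stands is what is written: the change-on-prior-change form, and a directional inference resting on two checks that both run one way. That is a stated model, not a missing detail.

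A reader might also infer that same-session reporting forces a spurious negative coefficient. It does not. The slope is about zero when the scales are uncorrelated within session, the artefact is positive for mood, and a sizeable true effect can keep its sign. Slopes of -rho/2 belong to the extreme case with no carry-over between sessions.

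Nor does the bias manufacture support for hypothesis 4; it works against it for all three predictors. The lag model is also only one of two timeline checks for one hypothesis. The baseline regressions and the concurrent growth model are unaffected.

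Finally, the obvious repairs are unsafe. This objection stands and shapes the fix.

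**Conclusion.** The point holds in bounded form. The described model biases the lagged coefficient opposite to the same-session association wherever that association outweighs the lagged ones. It can therefore mask or reverse a true lagged effect, and its one-way form cannot carry the directional claim.

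With no lagged effect, same-session correlation 0.2 to 0.6 and autocorrelation 0 to 0.3, the expected slope is -0.07 to -0.30 (sign reversed for mood), significant in roughly half to all trials of the planned size. A true effect of 0.15 can appear as 0.03.

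These figures assume 14 equally spaced sessions, no missing data and equal SDs in the no-effect formulas. The correlations, autocorrelations and error shares are assumptions, because the article gives none of them. The direction of the bias is firmer than its size.

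**What to change.** Replace the change-on-change model with a bivariate within-person lagged-level model. Regress PTSD(t) on PTSD(t-1) and predictor(t-1), with latent person means, a time trend, and session-specific measurement error allowed to correlate across scales within a session. Estimate the mirror path, predictor(t) on predictor(t-1) and PTSD(t-1), in the same model, and report both. Claim that predictor change leads to PTSD change only if the forward path holds and clearly exceeds the reverse path, compared on a within-person standardised scale. State the expected sign for each predictor, since mood is scored in the opposite direction.

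Do not rely on raw prior PTSD or previous PTSD change as the only correction, nor on centring at observed person means without a session-error term.

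The cost is a somewhat more complex model with wider intervals. The session-error part may be weakly estimated if scores carry over little between sessions; the full model was not itself simulated here, so a short simulation before lock would be prudent. No new data are needed, and the Discussion states that no analysis has yet been run, so the change can be made before results are known.
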